## Abstract

**Introduction:**

Patients frequently face excessive waiting times for specialist medical outpatient clinics, negatively impacting health outcomes. Previous research has demonstrated that translation of demand-driven strategies incorporated within the evidence-based Specific Timely Assessment and Triage (STAT) model effectively reduces wait times in a range of healthcare settings. We outline the study protocol for a hybrid type II implementation effectiveness study, using a stepped wedge cluster randomised controlled trial design, to evaluate whether the STAT model can be implemented in specialist medical clinics and reduce waiting times.

**Methods:**

The Waiting List Evidence to Support Specialist clinics (WaitLESS) trial will implement STAT in eight clinical specialties (clusters) offering outpatient medical care at a metropolitan health network in Melbourne, Australia. After a 6 month pre-implementation period, clusters will be randomised to implement the STAT model, two clusters at a time at 3-month intervals, with a minimum 6-month follow-up period, following the STAT model’s five-step implementation process: (i) analyse historical clinic demand data, (ii) model supply/demand, (iii) implement target interventions to address existing backlogs, (iv) protect capacity for new patients to align with demand and (v) implement tailored strategies to enhance patient flow. Strategies will be implemented collaboratively by researchers and clinical teams. The trial will measure both effectiveness (reductions in waiting time and patients on the waiting list) and implementation (fidelity, adoption, acceptability, feasibility, appropriateness and cost) outcomes, using quantitative healthcare data and qualitative data from staff and patients.

**Analysis:**

Linear mixed-effects models will be used for analysis of the primary effectiveness outcome of waiting time from referral to first appointment, with time point and time since intervention as factor variables. Implementation outcomes will be analysed descriptively, with qualitative data mapped deductively to the Consolidated Framework for Implementation Research. A cost of implementation and cost-effectiveness analysis will be completed from the health service perspective.

**Trial registration number:**

ISRCTN15820171.

STRENGTHS AND LIMITATIONS OF THIS STUDYRobust design, using a stepped wedge cluster randomised controlled trial to test a service-level intervention to reduce waiting times in specialist medical outpatient services.Inclusion of implementation outcomes and a health economics analysis will provide valuable insights into how the model is implemented, reasons for success or failure, costs of implementation and cost-effectiveness.The intervention (the Specific Timely Assessment and Triage (STAT) model) brings together evidence-based principles into one structured, step-by-step package that is described using the Template for Intervention Description and Replication checklist for future replication.Lack of direct measurement of individual patient health outcomes could be considered a limitation. However, we will capture qualitative data on patient experience as well as health service use during the periods before and after the index outpatient appointment as a proxy indicator of changes in health status.

## Introduction

 Outpatient clinics providing access to medical specialists are a pivotal part of health systems around the world. These services enable diagnosis and specialist care, reduce reliance on inpatient services and support general practitioners to manage complex health conditions in the community.^1^ However, growing demand for specialist services, driven by an ageing population, increasing prevalence of chronic disease and consumer expectations, is driving long waiting lists for specialist clinics.^2–4^ While these delays are often viewed as an inevitable and intractable problem in the delivery of healthcare, they contribute to increased healthcare costs, psychological distress and poorer health outcomes.^5–7^

The mechanism of delivery of these services (described in this paper as ‘specialist clinics’) differs across countries and healthcare systems, spanning public and private funding systems. Publicly funded specialist clinics are often provided free or at low cost within universal public healthcare systems, such as those seen in Australia, the UK, New Zealand and Canada, but long wait times are common.^3
8^ However, access challenges for medical specialists have also been reported to be prevalent in systems with predominantly private funding, particularly for people experiencing social disadvantage.^9^

Despite evidence demonstrating that health service waiting lists can be reduced through service-level reform^10–14^ or policy interventions,^15^ long waiting times for specialist clinics remain a public concern.^16^ Data from Australia show half of patients wait more than 50 days across all specialties for a first appointment, and 10% of patients wait more than a year.^3
17^ The link between delays in access to care and poorer health outcomes has been well-established for a wide range of conditions.^7
18–21^ Furthermore, patients on outpatient waiting lists feel ‘forgotten’, are unable to plan for the future, experience deterioration in their health, are angry with the system and express a fear of ‘dying on the waiting list’.^5^

Strategies commonly used for managing waitlists and reducing waiting time in health services are often ineffective. Injections of resources to temporarily boost the supply of health services without a subsequent change in service delivery have only short-term effects, with waiting lists inevitably growing back over time.^4
14
22
23^ Long-term supply-side solutions are often hampered by workforce shortages and lack of funding. Triage systems are often used as a demand management tool but frequently lack reliability and contribute to inefficiencies by directing resources away from frontline care while doing little to solve the underlying problems contributing to the existence of the waiting list in the first place.^24^ Service providers are left with an impression that waiting lists are inevitable and give up on seeking solutions.^25^

However, there are a range of strategies that can be introduced by health services to reduce outpatient waiting times. Examples of principles of successful strategies include balancing supply and demand, improving efficiency of processes and protecting capacity for new patients and role substitution, in which alternative health providers undertake roles otherwise conducted by more specialised professionals.^10
11
13^ These strategies have been used in various combinations, often tailored to local context.^13^ This evidence is supported by consistent findings from a large number of studies, although limited by a predominance of single-group, observational study designs.^13^

The Specific Timely Assessment and Triage (STAT) model brings together several of these evidence-based principles into a step-by-step intervention and has led to sustainable reductions in wait times across a broad range of settings.^26–30^ STAT begins with analysis of supply and demand, followed by short-term, targeted interventions to reduce the existing waitlist and then protecting capacity specifically for new patients to enable access at the rate of arrival. New patients are booked in immediately for a first appointment without using a waiting list, and decisions about subsequent care are made by the treating clinician with consideration of patient need and service capacity. To date, the STAT model has been trialled in a range of allied health, community health and multi-disciplinary clinic settings, including a multi-site stepped wedge cluster randomised controlled trial resulting in a 34% reduction in waiting times (IRR 0.66, 95% CI 0.51 to 0.85).^27^ Specialist clinics share common features with other types of ambulatory services but also have unique challenges; they tend to see very large volumes of patients with mixed acuity, cross multiple funding systems and many face much larger backlogs of waiting patients than have been addressed in previous trials. Early success in a single pilot study in a single specialist outpatient clinic that almost eliminated a waiting list of 600 patients and sustained the service with minimal waiting lists over 4 years suggests it is feasible to apply the STAT model to specialist clinic settings, but further research is required to see whether it can be implemented at scale.^31
32^

This hybrid type II study using a stepped wedge cluster randomised controlled trial design aims to determine (i) whether the STAT model is effective in reducing waiting lists and wait times for specialist medical clinics and (ii) whether it can be successfully implemented across multiple services, including an embedded health economic analysis to determine the cost of implementation and cost-effectiveness of the model.

## Method

### Setting

The trial will take place at Eastern Health, a large network of metropolitan services in the eastern suburbs of Melbourne, Australia, providing publicly funded health services to a diverse community of approximately 892 000 people, including a high proportion (32%) of residents born overseas. Eastern Health offers a broad range of services, including emergency care, surgery, maternity, palliative care, mental health, drug and alcohol services, residential care and community health, delivered across three tertiary hospitals, two sub-acute inpatient services, a small community hospital, a day surgery centre and more than 30 community sites. The inclusion of a single health service could be seen as a limitation, but the size of the health network and its operation across multiple sites spanning a diverse geographical catchment provide confidence in the applicability of the findings to a broad range of health settings.

Eastern Health operates a comprehensive network of specialist medical clinics, providing expert care across a broad range of medical disciplines. Patients are typically referred to these clinics by general practitioners, specialists or hospital-based clinicians. Referrals are made electronically, then triaged by clinicians and assigned a priority category. Urgent referrals may be booked directly into appointments, while routine referrals are waitlisted until an appointment becomes available. Waiting times vary from weeks or months to several years.

### Design

We will conduct a hybrid type II effectiveness-implementation trial. Hybrid type II trials are designed to test both the clinical effectiveness of an intervention and the implementation strategy and can be effective in supporting more rapid research translation.^33^ This approach is well suited to this study, given that there is strong face validity for the intervention, strong indirect evidence and preliminary direct evidence of effectiveness, existing ‘implementation momentum’ (eg, stakeholder support), low risk and reasonable expectation that the implementation strategy is appropriate for this setting.^34^ The trial has been prospectively registered with the ISRCTN (UK National Clinical Study Register), registration number ISRCTN15820171 and reported in accordance with the STaRI checklist.

The design incorporates a stepped wedge cluster randomised controlled trial measuring both effectiveness and implementation outcomes with an embedded health economics evaluation to determine the cost of implementation and cost-effectiveness from the health service perspective. The health service perspective was selected as study findings will be primarily of interest to, and used by, providers of specialist clinics to support decision-making and appropriate allocation of funding.

The stepped wedge cluster randomised controlled trial (figure 1) will sequentially introduce the STAT intervention to clinics provided within eight speciality areas (clusters) in random order. Control data will be collected for 6 months (commencing 31 March 2025), after which the STAT model strategies will be introduced sequentially to two clusters within each step, with new steps commencing at 3-month intervals. There will be a 6-month period for implementation at each cluster, followed by commencement of collection of post-implementation data. The post-intervention data collection period for all clusters will conclude on 27 June 2027. While the design carries some risk of contamination and implementation fatigue due to the possibility of some of the same staff working across different clusters, this will be minimised through the inclusion of a diverse range of clinical specialties and a structured implementation process supported by project staff. Data will be collected for at least 6-month post-implementation at all clusters (figure 1). The primary effectiveness outcome will be a comparison of waiting (measured as time to first appointment and number of people on the waiting list) across the pre- and post-implementation periods. Implementation outcomes will be organised under six domains of acceptability, adoption, appropriateness, feasibility, fidelity and costs using a mixed-methods approach incorporating qualitative data and routinely collected healthcare data.

**Figure 1 F1:**
[figure not shown]
Implementation plan for a stepped wedge cluster randomised controlled trial.

### Inclusion criteria

Included services (clusters) will be medical specialties (n=8) offering outpatient clinics at Eastern Health that have waiting lists with a minimum average of 12 weeks’ waiting time to first appointment and/or more than 200 people without appointments allocated. Given that referrals to a given specialty enter through a single waiting list but can then be distributed across multiple clinics (eg, operating at different locations across the health service), the clinics operating under each specialty will collectively form one cluster in the trial. Cluster selection will be decided in consultation with the medical directors of the clinics and senior leaders of the programme responsible for delivery of specialist medical clinics, based on (i) commitment from clinical leaders to initiate innovative changes to practice; (ii) potential for flexibility in service delivery (eg, variability in length or frequency of appointments, use of telehealth, involvement of nursing/allied health professionals in care) and (iii) the aim to include clusters across a spread of specialties.

Individual participants will include staff and patients who will contribute data to implementation outcomes. All staff working in the selected specialty areas during the study period (including medical staff, nursing and allied health staff, clerical staff and managers) will be invited to contribute to service reforms aligned with the intervention and be eligible to participate in focus groups. While some clinical specialties employ large numbers of sessional medical staff, we aim to include 4–8 participants per focus group for each clinic who are representative of key stakeholder groups and have detailed knowledge of clinic operations. For semi-structured interviews with patients, eligibility criteria will include the following: adult patients (or caregivers of children) who have been triaged as routine patients, recent attendance at a first appointment with a participating clinic; capacity to provide consent and sufficient oral communication capacity to participate in an interview (with an interpreter if required). Purposive sampling will be used with the aim of including a diverse range of participants.

### Randomisation and masking

The eight clusters will be randomly paired, and then the four pairs will be randomised for order of intervention. Randomisation will be undertaken using a random number sequence, computer-generated by an external clinical trial support service not involved in the study and blind to the identity of the participating medical specialties. Researchers and participants will not be informed which clusters will form the next intervention pair until 3 months prior to commencement of their implementation period. Clinic patients will not be aware of the study, and routinely collected data contributing to the primary outcome measure (referral and appointment dates used to calculate waiting time, patients allocated to the waiting list) are collected by a centralised data management service within the health organisation independent from the research team. Patients attending the service and the health service staff collecting the primary outcome can therefore be considered blinded to the intervention.

### Intervention and implementation strategy

The intervention will consist of a suite of service redesign initiatives based on the STAT model. During the implementation period, staff within each cluster will be trained in the STAT model in workshops of 1–4-hour duration (tailored for teams and individuals according to prior knowledge of STAT and role within the service, with options for flexible delivery), led by investigators [name] and [name]. This training was developed at Eastern Health/La Trobe University and has been delivered to more than 1000 clinicians across Australia from more than 100 services over the past 4 years.^35^

Following training, the clinic staff will be guided through each of five steps of the STAT model: (i) analyse clinic supply and demand data, (ii) model supply and demand at the clinic, (iii) targeted interventions to address the existing backlog (using a comprehensive waiting list audit supplemented by targeted, short-term supply-side interventions), (iv) protect capacity for new patients to align with demand and (v) implement tailored strategies to enhance patient flow. Step 5 will incorporate enhanced clinic coordination, alongside other strategies that could include (but are not limited to) productivity improvements (such as reducing failure-to-attend rates), multi-disciplinary approaches to service delivery and partnerships with patients and primary care (table 1).

**Table 1 T1:** Key WaitLESS intervention activities and corresponding resources

Key activities	Resources provided
**Staff training** in the principles of the STAT model	Four-hour workshop training provided by members of the research team
**STAT Step 1:** Retrospective collection and analysis of clinic data—typical supply and demand over past 2 years	Support from research team/project manager
**STAT Step 2:** Model supply and demand; determine how much capacity needs to be protected for new patients to maintain flow at the rate of demand	Support from research team/project manager
**STAT Step 3**: Address existing backlog. Example activities: Comprehensive waitlist audit: cleaning the list, including checking for errors and calling/messaging patients to determine need Short-term increase in supply Grouping similar patients for targeted interventions	Clerical assistance for auditing Some funding for additional short-term clinic supply
**STAT Step 4:** Redesign clinic templates to align with demand	Support from research team/project manager
**STAT Step 5:** Tailored interventions to enhance patient flow: Enhanced clinic coordination Other tailored strategies, such as multi-disciplinary approaches, partnerships with consumers and primary care	Part-time clinic coordinator during implementation and post-implementation periods Support from research team/project manager

STAT, Specific Timely Assessment and Triage; WaitLESS, Waiting List Evidence to Support Specialist.

Implementation of the intervention will be supported by the project team (including chief investigators based at the health network, as well as a project manager and research assistant), who will meet regularly with key stakeholders during the implementation period to facilitate the changes. Project funding will be used to employ a part-time clinic coordinator (12.5 hours per week) during the pre- and post-implementation period at each participating clinic (nursing or allied health background, as appropriate to the health conditions addressed by each clinic). Intervention elements are further described in table 2, using the Template for Intervention Description and Replication checklist.^36^

**Table 2 T2:** Intervention described using the TIDieR checklist

Name	STAT model for reducing healthcare waiting times
Why/background	To address long waiting lists/waiting times for specialist clinic appointments.
What	The STAT model for managing demand for health services Five-step implementation process: Collect historical data on supply and demand for the services Analyse the supply/demand relationship—determine the throughput rate required to operate at the pace of demand Address the existing backlog using targeted strategies Comprehensive waiting list audits Short-term supply-side interventions Align clinic templates with demand and protect sufficient capacity for new patients Tailored strategies to enhance patient flow, including improved clinic coordination, efficiency measures, innovations to models of care and improved partnerships.
Who	Research team working in collaboration with clinical leaders, specialist medical staff, nursing/allied health staff and clerical support teams. Research team includes a project manager (0.6 EFT), research assistant/data manager (0.8 EFT) and two senior researchers (0.2 EFT each) actively contributing to the implementation process. A clinical coordinator employed (0.25 EFT) also employed at each clinic during the implementation/post-implementation periods to support implementation and embed changes
How	Research team analyses supply/demand data and provides training in the STAT model. Teams and researchers work collaboratively to work through steps 3–5 of the model and implement changes Regular meetings between researchers and clinic teams with support from clinic coordinator to implement process changes
Where	Large metropolitan health network in Melbourne Eight medical clinical specialty areas operating specialist medical clinics with waiting times of >3 months or with >200 patients waiting
When and how much	Six-month implementation period for each specialty Two new specialties commence at each step (every 3 months), four steps in total
Tailoring and modifications	Interventions tailored to each clinical specialty within the overall structure and principles of the STAT model
How well (fidelity)	Fidelity will be judged by the extent to which each of the STAT steps are completed Analysis of supply and demand completed, and the number of new appointments required to keep pace with demand calculated (STAT steps 1 and 2) Active measures taken to reduce the size of the existing waiting list Appointments for new patients protected in clinic schedules, based on demand Strategies implemented to enhance patient flow

EFT, equivalent full-time; STAT, Specific Timely Appointments for Triage; TIDieR, Template for Intervention Description and Replication.

### Data sources

Data will include routinely collected health data, qualitative data from staff and patients and cost and revenue data for the participating clinics.

#### Routinely collected healthcare data

Effectiveness outcomes will be drawn from routinely collected healthcare data, collected from the records of patients seen in the clinic during the pre-implementation and post-implementation periods (n>5600 patients) and de-identified for analysis. Clinic data will also be used for implementation outcomes, such as the number of patients scheduled and seen and failure to attend rates. Fields for datasets are included in online supplemental file A.

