### Sample size

A minimum average of 400 referrals is expected to be received for each included specialty annually (100 per quarter), resulting in at least 700 patients across the pre- and post-implementation periods for each cluster (minimum total sample, n=5600). With four steps and eight clusters (two clusters per step), this stepped wedge design will be well powered to detect even small-to-moderate effect sizes. For a mean difference of 0.25 SD in waiting time and a conservative ICC of 0.1, with at least 60 referrals per cluster per 3-month time period (which is less than the pro-rata expected number annually), this design is powered at approximately 90% to sufficiently detect a difference at a 5% level of significance.^38
39^ Again, under conservative assumptions, power for detecting significant differences for our secondary outcomes (eg, an increase in the proportion of urgent patients seen within 30 days from 80 to 90%) exceeds 90%. Compared with our findings from STAT implementation in community outpatient services,^27^ our power and sample size assumptions are chosen conservatively to more than compensate for additional heterogeneity or other differences in the specialised clinic setting.

The sample size for quantitative implementation outcomes is based on the duration of the intervention and length of the waiting lists of the included services. The sample size for the qualitative analysis is considered feasible and expected to be sufficient to reach information power.

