#### Effectiveness

Linear mixed effects models will be used to analyse data related to the primary outcome with time-point (time since trial start) and time since intervention as factor variables. This allows for the expected nonlinear change over time, as well as an analysis of persistence of intervention and time-averaged intervention effects following the service redesign, consistent with recommendations.^40^ Generalised linear mixed effects models will be used to analyse the secondary outcomes (binomial for proportions and negative binomial for counts to allow for over-dispersion). A random effect for the clinic will be used for all models to account for clustering. Visual diagnostics will be used to assess model assumption validity, and transformations of outcomes or robust estimators will be used as needed. Adjusting for and analysing the association between covariates (eg, referral source and demographic data, including potential indicators of disadvantage such as need for interpreters) and outcomes will also be completed by including these in the mixed-effects models as predictors. Given the small number of clusters, the Kenward-Roger small-sample correction will be used for the df for inference of the fixed effects.^41^

In the event of any system-wide (eg, pandemic) and within-cluster notable disruptions (eg, staffing issues) that are not adequately captured by the baseline random-effects structure and residual variation, a disruption indicator variable will be used for the disrupted time period. This model of adjustment to disruption can also be included as an indicator within affected clusters only. As an additional sensitivity analysis, within-cluster time-series analyses will be conducted to account for localised temporal disruptions while assessing the persistence of intervention effects. R V.4.4.1 (or a newer version if available) will be used for the analyses.

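### With implementation-quarter records left out, only quarter 5 compares control with post-implementation clusters, and power on the stated calendar is well below 90%

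*Protocol article*

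**What the plan says.** The Design section starts control data on 31 March 2025, gives all clusters six months of control, and brings in pairs of clusters "with new steps commencing at 3-month intervals". It continues: "There will be a 6-month period for implementation at each cluster, followed by commencement of collection of post-implementation data". Collection ends for everyone on 27 June 2027. The section frames the primary comparison as pre- against post-implementation.

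Under Routinely collected healthcare data, the effectiveness outcomes are "collected from the records of patients seen in the clinic during the pre-implementation and post-implementation periods". The Sample size section expects 100 referrals per quarter and at least 700 patients per cluster across the pre- and post-implementation periods, 5,600 in total. It states about 90% power for 0.25 SD at ICC 0.1, with 60 referrals per cluster per quarter and 5% significance.

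The Effectiveness analysis uses a linear mixed model with "time-point (time since trial start) and time since intervention as factor variables", a random effect for clinic, and the Kenward-Roger correction.

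**The concern.** A stepped wedge with calendar time as a factor learns about the intervention from quarters in which some clusters are under control and others are post-implementation. The steps are three months apart but each cluster spends six months in implementation. If those six months are removed, almost all overlap between the two conditions goes with them.

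Two things are at stake. First, the primary effect hangs on one calendar quarter and four clusters, so it is fragile. Second, the power calculation may describe a wedge without this gap. The omitted data are not hard to get: Randomisation and masking says that the referral and appointment dates are held by a central data service.

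**Working it through.** **Calendar.** 31 March 2025 to 27 June 2027 inclusive is 819 days = 9 × 91, so nine 13-week quarters, matching the 27 months under Health economics data. C = control, I = implementation, P = post:

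| Pair | Q1 | Q2 | Q3 | Q4 | Q5 | Q6 | Q7 | Q8 | Q9 |
|---|---|---|---|---|---|---|---|---|---|
| 1 | C | C | I | I | P | P | P | P | P |
| 2 | C | C | C | I | I | P | P | P | P |
| 3 | C | C | C | C | I | I | P | P | P |
| 4 | C | C | C | C | C | I | I | P | P |
| Clusters C/P | 8/0 | 8/0 | 6/0 | 4/0 | **2/2** | 0/4 | 0/6 | 0/8 | 0/8 |

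Every cluster has 7 quarters in C or P. 7 × 100 = 700 and 8 × 700 = 5,600, exactly the protocol's counts. Trial governance places the review of the first two clusters in time period five, which fits their first post quarter.

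**Identification.** Without the I cells, only Q5 (30 March to 28 June 2026) holds both conditions. Drop Q5 and a constant-effect model has 8 quarter columns plus 1 treatment column = 9, with rank 8. The time-since-intervention model has 8 + 5 = 13, with rank 12. The effect is not estimable in either. With Q5 kept, the generalised least squares (GLS) weights for a constant effect are +0.5 or −0.5 for each Q5 cluster and at most 0.095 in size elsewhere. Those other cells adjust for cluster differences. Later effects are chained on: Q6, for example, compares pair 1 in its second post quarter with pair 2 in its first.

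**Variance and power.** Take cluster-quarter means with total variance 1, cluster variance 0.1 and sampling variance 0.9/m. Then V = 0.1·J + (0.9/m)·I within cluster, Var = l′(X′V⁻¹X)⁻¹l, and power = Φ(0.25/SE − 1.96).

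*The protocol's figure.* A wedge with the gap closed up, so that implementation takes no calendar time (7 periods, m = 60), has SE 0.0645. Power is 97.2% by the normal approximation and 89.4% with t on 6 df. The latter matches the stated 90%, though this does not prove how that figure was obtained.

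*True calendar, I quarters left out.*

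| Model | m | SE | 0.25/SE − 1.96 | Power |
|---|---|---|---|---|
| Time-averaged (protocol's model) | 60 | 0.1829 | −0.593 | 27.7% |
| Time-averaged | 100 | 0.1424 | −0.204 | 41.9% |
| Constant effect | 60 | 0.1336 | −0.089 | 46.5% |
| Constant effect | 100 | 0.1036 | 0.453 | 67.5% |

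Hand check for a constant effect at m = 60: even with cluster levels known exactly, the Q5 contrast has variance 0.015/2 + 0.015/2 = 0.015. That gives SE 0.1225 and power Φ(2.041 − 1.96) = 53%. No adjustment from other quarters can beat this ceiling.

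*True calendar, I quarters kept as two extra levels.*

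| Model | m | SE | Power | Variance ratio, out/kept |
|---|---|---|---|---|
| Time-averaged | 60 | 0.1542 | 37% | (0.1829/0.1542)² = 1.41 |
| Time-averaged | 100 | 0.1204 | 55% | 1.40 |
| Constant effect | 60 | 0.0998 | 71% | (0.1336/0.0998)² = 1.79 |
| Constant effect | 100 | 0.0775 | 90% | 1.79 |

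Both models now stay estimable with Q5 removed (full rank: 11 of 11 and 15 of 15).

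*With a cluster-specific random implementation effect.* Add its variance to V for pairs of I cells in the same cluster. The protocol gives no value for its SD, so I assume 0.1 and 0.25. Time-averaged power becomes 34.5% and 31.6% at m = 60, and 50.5% and 46.8% at m = 100. Constant-effect power becomes 64% and 56%, and 83% and 76%.

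**The case against.** Four points deserve weight.

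- **The exclusion is inferred.** No sentence says that implementation quarters are dropped from the model, and the design figure is not available here. The data-source wording, the pre/post comparison and the 700 count all point the same way, so the reading is sound for waiting time. A reader might extend it to the number of people on the waiting list. The text does not support that: the count is measured weekly, with no stated restriction to pre and post periods.
- **The larger gains belong to another model.** The move from 47% to 71% is for a constant effect. Under the time-since-intervention model that the protocol names, the gain is from 28% to 37%. A reader might infer that keeping the quarters rescues the stated power; it does not.
- **Omitting a transition period is a recognised choice.** Backlog clearance brings in long-waiting patients and can raise recorded waits in those quarters. Starting waits run from weeks to several years and the interventions are tailored, so the shift may differ by specialty. Two common implementation levels are therefore a stronger assumption than common post-implementation levels, and an error in them would pass through the quarter effects into the reported effect. This stands and shapes the fix.
- **Disruption is provided for.** A reader might infer that a local problem in one quarter-5 cluster simply becomes the result. The analysis section offers a disruption indicator, including for affected clusters only, and within-cluster time-series sensitivity analyses. These soften the point but leave the primary model dependent on quarter 5: an indicator covering both quarter-5 clusters of one condition would absorb the only concurrent contrast.

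**Conclusion.** The point holds as a should-fix. If waiting-time records from the implementation quarters are left out, as the protocol reads, one quarter of nine identifies every contrast with control, two clusters against two. The effect remains estimable, and the other quarters still adjust for cluster differences and give the later effects their shape, so it would be too strong to say that four cluster-quarters alone decide the trial.

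The stated 90% does not hold on this calendar: about 28% at 60 and 42% at 100 per cluster-quarter for the time-averaged effect, and about 47% and 68% for a constant one.

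These figures assume a two-sided 5% test, equal cluster-quarter sizes, a cluster random intercept only, and a normal reference distribution. Relaxing the last two lowers power. With t on 6 df, as a rough stand-in for Kenward-Roger, the constant-effect figure at 60 falls from 46.5% to 35.1%. With a cluster autocorrelation of 0.95 it falls to 36.8% (normal approximation). The result is not driven by the ICC: constant-effect power at 60 stays between 44% and 51% for ICC 0.01 to 0.2.

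**What to change.** 1. Extract the same routine fields for the implementation quarters.
2. Keep them in the primary mixed model as two separate levels of time since intervention (first and second implementation quarter) that do not enter the reported effect. The estimand remains the post-implementation effect; the added cells help to estimate the calendar-quarter effects.
3. Allow a cluster-specific random implementation-period effect, because backlog clearance differs by specialty.
4. Report the analysis without these quarters as a sensitivity analysis, and state that quarter 5 is its only concurrent contrast.
5. Recalculate the Sample size statement on the nine-quarter calendar and for the model to be fitted, with the small-sample correction. Say which effect, time-averaged or constant, the power refers to.

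The cost is 16 cluster-quarters × 100 = about 1,600 more routine records and a short change to the data-source, analysis and sample-size text. The remaining downside is some assumption about implementation-quarter effects, which the random effect weakens at the price of part of the gain.
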